#### Multimodal integration

2.5.6

The data collected through EEG, ETS, motor tests (LSPT and Y-SART) and subjective measures (FAS and VAS) will be integrated into a multimodal and correlational analysis, with the aim of identifying convergent patterns of response to mental fatigue. This approach allows for the simultaneous examination of cortical, oculomotor, behavioral, and perceptual changes, providing a more complete characterisation of the neurophysiological and functional mechanisms underlying mental fatigue in athletes. Recent studies demonstrate that the integration of multiple measurement modalities, such as EEG, ETS, and performance parameters, improves sensitivity in detecting states of fatigue and understanding its cognitive and motor manifestations (62, 86, 87).

Multimodal analysis will be performed both at the group level (experimental vs. control) and at the intra-subject level (pre- vs. post-intervention). Comparisons between groups will help determine the discriminatory power of each modality in detecting fatigue, while intra-individual assessments will examine how each marker evolves in response to cognitive load. In addition to identifying response patterns across modalities, the study will examine associations between modalities, such as correlations between EEG (e.g., alpha/theta power), ETS markers (e.g., blink rate, saccades), motor performance metrics (LSPT and Y-SART), and subjective measures (VAS, FAS). This integrated framework allows us to assess whether neurophysiological changes are aligned with behavioral and perceptual data, increasing the validity of fatigue assessment.

This multimodal integration also enables the identification of potential short-term compensatory responses. For instance, preserved motor performance accompanied by increased perceived fatigue or altered cortical and oculomotor activity may reflect greater cognitive effort to maintain task execution under mental fatigue. Such patterns may indicate adaptive adjustments in response to cognitive overload, even in the absence of overt performance decline.

This triangulation approach is expected to reveal composite markers of mental fatigue, allowing us to combine EEG data, eye-tracking parameters, motor performance outcomes, and self-reported measures into multidimensional fatigue profiles. Such profiles may inform the development of more accurate monitoring protocols in high-performance environments.

Ultimately, the combined interpretation of these results will provide an integrative understanding of the neurocognitive and behavioral mechanisms underlying mental fatigue in football. This holistic view may contribute to practical strategies for detecting, monitoring, and mitigating fatigue in sporting contexts that require sustained attention and decision-making under pressure.

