### Sample

2.2

Sample size was calculated using G*Power 3.1.9.7 software (41), considering a repeated measures ANOVA design with two groups (experimental *vs.* control) factors, and two measurement times (pre *vs.* post). The estimated minimum sample size at alpha 0.05 and statistical power of 80%, for moderate effect size (f = 0.25), was approximately 34 subjects (17 per group). At baseline, participants will be pre-screened using an online questionnaire to determine eligibility.

The inclusion criteria were: (i) minimum age of 18; (ii) at least one year of competitive football experience; (iii) no eye problems that impair vision; (iv) no history of neurological injuries; (v) abstinence of caffeine, alcohol and intense physical activities in the previous 24 h before each experimental session; (vi) having slept for at least 7 h the night before. On the other hand, the exclusion criteria were: history of neurological injury; uncorrected vision problems; diagnosis of psychological disorders; use of psychoactive substances in the last 24 h before the experimental sessions; any form of nystagmus for electrophysiological contraindications for electrophysiological recording. The operationalization and description criteria are summarized in Table 1.

**Table 1 T1:** Sample operationalization and description criteria.

Topic	Description	Operationalization
Age	Minimum age of 18 years	Participants aged 18 years or older. There is no maximum age limit stipulated in the protocol.
Gender	Gender balance	Sample of 24 men and 24 women, in equal number for experimental and control groups.
Competitive experience	Minimum of 1 year of competitive experience	Football players with a minimum of 1 year of regular practice in competitive condition
Health condition	No conditions preventing the practice of sport	Individuals with a history of neurological injuries, uncorrected visual problems, diagnosed psychological disorders, use of psychoactive substances in the last 24 h, or any clinical limitation to physical exertion will be excluded. Pregnant women will also be excluded.
Legal and ethical criteria	Compliance with current regulations	The study complies with the GDPR and the provisions of Decree-Law No. 5/2007, ensuring that all participants meet the legal and ethical conditions for physical exercise.

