#### Technical and motor performance

2.5.3

Technical and motor performance will be assessed using the LSPT and the Y-SART, using Witty SEM indicators (Microgate, Bolzano, Italy). These instruments allow the effects of mental fatigue on technical execution, reactive agility and decision-making processes in a sporting context to be quantified with high temporal precision and reliability.

Comparisons between groups will examine whether the ST induces greater impairments in performance metrics compared to a cognitively neutral task. The LSPT will provide data on total execution time, technical penalties, and adjusted score, while the Y-SART will produce reaction and execution times in response to visual stimuli. These comparisons will elucidate the degree to which mental fatigue affects motor fluency, visuomotor coordination, and accuracy under pressure.

Intra-subject analyses in the experimental group will allow for the detection of performance deterioration caused by the ST. By comparing pre- and post-intervention scores on both the LSPT and Y-SART, this approach will help determine whether mental fatigue results in statistically significant reductions in motor and technical efficiency.

The associations between performance metrics and indicators of fatigue (e.g., VAS, EEG, and ETS) will also be examined to explore whether higher levels of perceived or physiological fatigue correlate with slower and less accurate performance. These relationships may help identify which dimensions of fatigue are most predictive of declines in physical performance.

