### Statistical analysis

2.6

All statistical analyses will be performed using IBM SPSS Statistics version 29.0 (IBM Corporation, Armonk, NY, USA), with a significance level set at 5% (*p* < 0.05). Descriptive statistics (mean, standard deviation, 95% confidence intervals, and range) will be calculated for all outcome variables, including EEG spectral powers, oculomotor parameters, motor performance scores, and subjective fatigue ratings. These data will be stratified by group (experimental and control) and time (pre- and post-intervention) and presented visually using box plots and line graphs to facilitate interpretation (88, 89).

To assess the effect of mental fatigue, paired t-tests will compare pre- and post-intervention results within each group, while independent t-tests will compare the experimental and control groups at each time point (88, 90). For EEG outcomes, repeated-measures ANOVA models will include Time (pre vs. post mental fatigue) and Recording Condition (eyes open, eyes closed, motor imagery) as within-subject factors, and Group (experimental vs. control) as a between-subject factor (88, 90). Assumptions of normality and sphericity will be evaluated prior to analysis, following established recommendations for repeated measures designs (88, 91). When sphericity is violated, the Greenhouse-Geisser correction will be applied. Effect sizes will be reported using eta squared (*η*^2^), interpreted according to Marôco (90) as small (<0.04), moderate (0.04–0.25), or large (≥0.25). Statistical power (π) will also be reported when applicable (92, 93).

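### Group mean comparisons and separate correlations are assigned to questions about discrimination and best prediction, with no discrimination estimate and no comparison between markers planned

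*Protocol article*

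**What the plan says.** Two aims in the protocol article go beyond asking whether the Stroop task changes an outcome.

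- **Discrimination.** Section 2.5.6 (Multimodal integration): "Comparisons between groups will help determine the discriminatory power of each modality in detecting fatigue".
- **Best predictor.** Section 2.5.3 (Technical and motor performance), on associations of performance with VAS, EEG and eye tracking: "These relationships may help identify which dimensions of fatigue are most predictive of declines in physical performance".

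Section 2.6 (Statistical analysis) supplies the tools. For the effect of fatigue, "independent t-tests will compare the experimental and control groups at each time point", alongside paired t-tests within groups, all at the 5% level. EEG also gets a repeated-measures ANOVA with time, recording condition and group. Associations are pairwise Pearson correlations, which the section also uses to look for predictive relationships. Eta squared is reported in three bands (below 0.04, 0.04 to 0.25, and 0.25 or more). Correlation matrices and regression models are to identify fatigue profiles; their outcomes and predictors are not given.

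Neither section 2.5 nor section 2.6 names a measure of discrimination with an interval, a paired comparison of two markers, or a test of the difference between two correlations.

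**The concern.** How well a modality detects fatigue, and which dimension predicts best, are questions about separation of individuals and about one marker relative to another. A t-test has equal means as its null hypothesis, and a Pearson test has zero correlation. Neither compares markers. If one modality reaches p < 0.05 and another does not, that is not evidence that the two differ. A significant mean difference also does not show that a marker is useful for classifying a single player.

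This is more than detail left to a fuller document, because the article itself attaches these methods to these aims. At stake is a secondary aim: statements that one modality detects or predicts fatigue better than another could rest on chance differences in significance. Section 2.5.6 says that the resulting profiles may inform monitoring protocols, and section 4 (Conclusion) links the findings to individualized monitoring.

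**Working it through.** **Inputs from the article (section 2.2, Sample).** The design is described as "considering a repeated measures ANOVA design with two groups" and two measurement times. Further: "The estimated minimum sample size at alpha 0.05 and statistical power of 80"%; "for moderate effect size (f = 0.25"); and the result "was approximately 34 subjects (17 per group"). Table 1 conflicts: "Sample of 24 men and 24 women, in equal number for experimental and control groups", that is, 48 in total and 24 per group. I use 17 per arm and keep 24 as a sensitivity case.

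**Assumptions (not in the article).** Two-sided tests; true effect d per marker; correlation between markers; repeated-measures correlation; normality with equal variances for AUC.

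**1. The plan's own figure.** For the group-by-time interaction, λ = f²·N·m/(1 − ρ), with m = 2 and df 1 and N − 2. At ρ = 0.5 and N = 34, λ = 0.0625 × 34 × 2 / 0.5 = 8.5 and power is 0.807, so 34 is reproduced. Other ρ give other totals (66 at ρ = 0, 16 at ρ = 0.8). On the change score the noncentrality is d²·n/2 = 8.5·d², so the planned effect equals d = 1.0 if ρ = 0.5.

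**2. Opposite verdicts for two equally good markers, 17 per arm.** Power p is from the noncentral t with 32 df and noncentrality d·√(17/2). AUC = Φ(d/√2). The chance that exactly one of two independent markers is significant is 2p(1 − p). For correlated markers it was simulated (40,000 runs).

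| d | AUC | p | Independent: 2p(1 − p) | Correlation 0.5 | Correlation 0.7 |
|---|---|---|---|---|---|
| 0.5 | 0.64 | 0.293 | 41% | 29% | 22% |
| 0.7 | 0.69 | 0.508 | 50% | 34% | 26% |
| 0.8 | 0.71 | 0.619 | 47% | 32% | 24% |
| 1.0 | 0.76 | 0.807 | 31% | 22% | 17% |
| 1.2 | 0.80 | 0.924 | 14% | 11% | 9% |
| 1.5 | 0.86 | 0.989 | 2% | not run | not run |

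The 50% at d = 0.7 is the peak, because 2p(1 − p) is largest at p = 0.5. With 24 per arm and d = 0.5, p = 0.396 and the figure is 48%.

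**3. What a just-significant difference means.** The critical observed d is t(0.975; 32)·√(2/17) = 0.699, so AUC = Φ(0.699/√2) = 0.69.

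**4. Separate correlations.** Two markers with the same true r to the outcome, correlated 0.3 to 0.5 with each other, give opposite verdicts as follows (simulated; the article does not say whether one arm or both enter).

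| True r | n = 17 | n = 34 |
|---|---|---|
| 0.3 | 26–30% | 34–41% |
| 0.4 | 34–40% | 32–38% |
| 0.5 | 37–44% | 17–20% |

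For an observed r of 0.5 the 95% interval (Fisher z) is 0.03 to 0.79 at n = 17 and 0.19 to 0.72 at n = 34.

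**5. Does banded eta squared settle it?** For two groups of 17, t² = 32·η²/(1 − η²). At η² = 0.04, t² = 1.33, d = t·√(2/17) = 0.40 and AUC = 0.61. At η² = 0.25, t² = 10.67, d = 1.12 and AUC = 0.79. The single moderate band therefore covers AUC 0.61 to 0.79.

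**6. With a direct comparison.** A paired contrast of two equally good standardised markers (simulated as a stand-in for a paired AUC difference; d 0.5 to 1.0, correlation 0 to 0.5) declares them different in 6 to 8% of trials. The standard error of one AUC (Hanley–McNeil, 17 per arm) is 0.096 at AUC 0.64, 0.092 at 0.69 and 0.083 at 0.76, so 95% half-widths are about 0.19, 0.18 and 0.16.

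**The case against.** The strongest reply is that no decision rule based on significance is written down. The wording is tentative in both sections: comparisons are to help, and relationships may help. A reader might infer that the trial will rank EEG, gaze, performance and self-report by which of them reaches p < 0.05. The article does not say so; section 2.5.6 looks for converging patterns and composite markers. This stands, and the figures in the working are therefore conditional on significance being used as the verdict. What remains is that the article sets the 5% level and gives no other way to judge a modality.

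Second, the planned output is not uninformative. Means, standard deviations, intervals and box plots by group are promised, and for two groups eta squared maps one-to-one to AUC under normality. That also stands. But the stated bands are broad, no interval for eta squared is mentioned, and its use with the t-tests is likely rather than explicit.

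Third, regression models are planned, so it would be wrong to infer that the search for the best predictor rests on correlations alone. The models are aimed at fatigue profiles, however, and no comparison of markers is attached to them. Their detail may fairly sit in a fuller document.

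Fourth, the effect sizes are assumed. Figures at d = 0.7 with independent markers are near the worst case, and markers of one induced state in the same players are unlikely to be independent. This stands, which is why a range is given. The t-test figures also do not fully describe EEG, which has its own ANOVA.

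**Conclusion.** The method does not match the stated aim. Tests of mean differences and of non-zero correlations are assigned to questions of discrimination and best prediction, and neither an interval for discrimination nor a comparison between markers is planned.

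If significance at 5% is used to judge modalities, two equally good markers at 17 per arm would get opposite verdicts in about 31 to 50% of trials when independent, and about 22 to 34% when correlated 0.5, for assumed d of 0.5 to 1.0. For strong independent markers the problem fades (14% at d = 1.2, 2% at d = 1.5). A result that only just reaches significance corresponds to an AUC of about 0.69, which is modest for detection in individuals.

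A reader might go further and conclude that the trial's main results or its size are compromised. They are not: the comparison of the two groups on each outcome and the calculation of 34 are untouched. This is an inexpensive improvement to a secondary aim.

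**What to change.** In sections 2.5.6 and 2.6:

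- Name one metric per modality in advance. Estimate discrimination as the AUC, with 95% interval, of its pre-post change for experimental versus control.
- Compare modalities by the paired difference in AUC (DeLong, or a bootstrap over participants), and compare predictors by a test of dependent correlations.
- Label these analyses exploratory. Claim that one modality is better than another only if the interval for the difference excludes zero.
- If this is not wanted, describe the group comparisons as sensitivity to the induction and drop the term discriminatory power.

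The AUC separates assigned groups, which is a proxy for being fatigued, and the text should say so. The change score for gaze needs eye tracking at the baseline passing test. Section 2.5.2 implies this, but section 2.4 mentions the recording only for the repeated tests, so it should be confirmed.

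The cost is a few lines of analysis on data that are otherwise already planned. The drawback is wide intervals: with a standard error of 0.092 for each of two AUCs, the difference would have to exceed 1.96 × 0.092 × √2 = 0.25 if the two estimates were independent, or 1.96 × 0.092 × √(2 × 0.5) = 0.18 if they were correlated 0.5 (assumed). The study will often be unable to rank modalities, and the report should show that plainly.

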To ensure data quality and reproducibility, EEG signals will undergo standardized pre-processing procedures. Data will be processed in MATLAB R2025a (MathWorks, Natick, MA, USA) using EEGLAB v2025. Continuous recordings will be visually inspected to identify gross artifacts or recording instabilities, and non-EEG channels will be removed prior to analysis. Signals will be band-pass filtered between 1 and 45 Hz using a zero-phase finite impulse response (FIR) filter and re-referenced to a common average reference. Artifact correction will be performed using Independent Component Analysis (extended infomax algorithm). Independent components will be automatically classified using the ICLabel plugin integrated in EEGLAB, and components identified as ocular, muscular, cardiac, line-noise, or other non-brain sources with high probability (≥0.90) will be removed prior to signal reconstruction. Channels exhibiting persistent excessive noise throughout the recording will be excluded from analysis. All preprocessing procedures will be applied consistently across participants and experimental conditions to ensure methodological standardization and internal validity.

Oculomotor activity will be recorded with the Pupil Core system (Pupil Labs GmbH, Germany), with sampling at 200 Hz. This equipment will allow the analysis of fixations, saccades, pupillary dilation or and blink rate, during the LSPT. The ETS was only applied in the LSPT, as it contains visual stimuli while performing gaze orientation and control of attention, appearing as especially appropriate to analyze gaze patterns (53). In addition, the LSPT is longer in duration, which makes it possible to collect consistent eye activity data. Vansteenkiste et al. (54) demonstrated a correlation between LSPT performance and gaze patterns in young players, reinforcing that this type of test is suitable for analyzing oculomotor metrics. In contrast, the Y-SART is a simple task and it presents brief visual stimuli, so the use of an eye-tracker is not justified. Recent research has demonstrated that motor skills (e.g., sprinting, changing direction, reactive strength) are the main determinant in performance on the Y-SART and is also affected by sensory/perceptual processes to a smaller extent or indirectly (55). The data will be processed with open-source software provided by the manufacturer.

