**Figure 3 F3:**
[figure not shown]
Schematic representation of the Y-SART, adapted from Yuan et al. (2).

After completing Phase 3, participants move on to Phase 4, where they perform the cognitive intervention defined by their group assignment, either the ST (experimental group) or a neutral task, such as reading magazines (control group). This is followed by Phase 5, which begins with participants completing the VAS again. Next, both motor tests are repeated, this time with continuous recording by the ETS. Finally, a second EEG recording is performed under the same conditions as in the initial phase, concluding the data collection session.

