##### Spectral analysis

2.5.1.2

EEG recordings will be acquired before (Pre) and after (Post) the performance of motor tasks, allowing the evaluation of the modulation of the global cortical state between moments and experimental conditions (experimental group vs. control group) (62). The EEG recordings will be obtained under resting-state conditions before and after mental fatigue induction. As no stimulus-locked tasks are included during EEG acquisition, event-related potential (ERP) analyses are not applicable within the present design. Although full-spectrum EEG data (delta, theta, alpha, beta, and low gamma) will be acquired across all electrodes, primary analyses will focus on theta, alpha, and beta power, given their consistent association with mental fatigue in previous literature (19, 61). Connectivity-based analyses are considered beyond the scope of this protocol and may be explored in future investigations. Between group comparisons will be conducted to detect whether the ST elicits greater alterations in alpha and theta power than the control condition, thus establishing whether different cognitive demands produce distinct neurophysiological signatures of fatigue. Comparisons between moments and groups will allow the identification of cortical alteration patterns associated with fatigue-related cognitive states. However, these oscillatory modulations will be interpreted in conjunction with behavioral, oculomotor, and subjective measures, acknowledging that EEG frequency changes reflect multifactorial neural dynamics rather than isolated biomarkers of mental fatigue (19, 60, 63, 64).

Within the experimental group, pre- and post-task EEG analyses will assess the impact of the ST on cortical activation, particularly changes in frontal theta and parietal alpha bands, to capture acute neurodynamic changes resulting from cognitive overload. Recent evidence by Krukow et al. (65) supports this approach, having demonstrated that mental fatigue states are reliably associated with altered EEG connectivity and spectral profiles, especially in the theta and alpha bands, during cognitively demanding tasks. These within-group comparisons aim to detect functional adaptations linked to increased attentional effort, executive control demands, and potential declines in motor preparation efficiency.

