##### VAS

2.5.4.2

The VAS for mental fatigue, applied immediately before and after the cognitive induction task (ST), captures acute fluctuations in the subjective perception of fatigue. This 100 mm continuous scale, anchored between “no fatigue” and “extreme fatigue”, is sensitive to short-term changes induced by cognitive load and task duration (84). Within the experimental group, VAS ratings will be compared pre and post ST to quantify the immediate impact of the intervention on mental fatigue.

In addition, associations between subjective fatigue and other objective markers will be explored. Specifically, post-intervention VAS results will be correlated with EEG spectral characteristics (particularly alpha and theta power), oculomotor parameters (blink rate, pupil diameter, saccadic dynamics, and fixations), and motor performance measures (LSPT and Y-SART). This approach allows us to determine whether higher levels of self-reported fatigue align with neurophysiological and behavioral indicators of reduced performance, providing a multimodal framework for validating the perceptual dimension of fatigue.

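### Section 2.5.6 reads the arm contrasts as each modality's power to detect fatigue, but the fixed Phase 5 order ties modality to time since induction and intervening exercise

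*Protocol article*

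**What the plan says.** Section 2.4 (Performance assessment, text after Figure 3) sets out what follows the 30-minute task in Phase 4:

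- "This is followed by Phase 5, which begins with participants completing the VAS again". Section 2.5.4.2 agrees, placing the VAS immediately before and after the induction task.
- The LSPT and the Y-SART come second, and eye tracking is used at this stage.
- The EEG comes last: "Finally, a second EEG recording is performed under the same conditions as in the initial phase, concluding the data collection session".

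Section 2.5.1.2 (Spectral analysis) confirms the place of the EEG: "EEG recordings will be acquired before (Pre) and after (Post) the performance of motor tasks".

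Section 2.5.6 (Multimodal integration) then says what the arm contrasts are for: "Comparisons between groups will help determine the discriminatory power of each modality in detecting fatigue". It describes the cortical, oculomotor, behavioural and perceptual changes as examined simultaneously. The order of measurement is not among the limitations in section 3.1.

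**The concern.** An arm contrast at a given moment shows how far the arms differ on that measure at that moment. It shows how well the measure detects induced fatigue only if the induced state is still present, and unaltered, when the measure is taken. Here the VAS is taken straight after induction, while the EEG follows two physically demanding tests.

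The article itself treats the state as short-lived. Section 2.3 chooses the VAS for its sensitivity to momentary variation, and section 3.1 confines the study to acute effects. If the state fades or is changed by exercise during Phase 5, a small EEG contrast would be read under section 2.5.6 as weak detection by EEG.

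The same section plans to read preserved motor performance with raised perceived fatigue as possible compensation. Fading between the VAS and the motor tests would produce that pattern too.

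**Working it through.** **Positions after induction (sections 2.3, 2.4, 2.5.1.2 and 2.5.4.2)**

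| Position | Measure | Motor tests since induction |
|---|---|---|
| 1 | VAS | none |
| 2 | LSPT with eye tracking, and Y-SART | in progress |
| 3 | EEG (five minutes) | both completed |

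Section 2.3 says "The ETS was only applied in the LSPT", so gaze and LSPT share a slot and there are about three positions, not one per modality. Section 2.4 can be read as applying eye tracking to both motor tests, and the two sections should be reconciled. Either way, every participant has the same order, so nothing in the data can separate modality from position. At baseline the EEG (Phase 2) comes before the motor tests (Phase 3), so the within-group pre-post EEG comparison also spans exercise.

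**The plan's own figure**

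Section 2.2 gives N = 34 for f = 0.25, alpha 0.05 and 80% power, with two groups and two times. The pre-post correlation is not stated; 0.5 is assumed here. For the Time by Group effect:

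λ = f² × N × m / (1 − ρ) = 0.0625 × 34 × 2 / 0.5 = 8.5, with 1 and 32 degrees of freedom.

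Power is 0.807, so 34 reproduces. The calculation uses one effect size and takes no account of when a measure is taken.

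**Illustration of what delay could do**

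Assumptions, none of them from the article: every modality is equally sensitive, with an arm difference of 1.0 SD at the end of induction; decay is exponential; exercise has no effect of its own. With 17 per arm, a two-sample t-test has noncentrality 1.0 × √(17/2) = √8.5 and 32 degrees of freedom. Power is therefore again 0.807, and a 1.0 SD difference matches the plan's own power level.

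- Difference at delay t: d(t) = 1.0 × 0.5^(t / half-life)
- Power: two-sided 5% t-test, noncentrality d(t) × √(17/2), 32 degrees of freedom
- AUC = Φ(d(t) / √2)

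| Delay | Half-life | d(t) | Power | AUC |
|---|---|---|---|---|
| 0 min | any | 1.00 | 81% | 0.76 |
| 20 min | 15 min | 0.40 | 20% | 0.61 |
| 20 min | 30 min | 0.63 | 43% | 0.67 |
| 20 min | 60 min | 0.79 | 61% | 0.71 |
| 20 min | 120 min | 0.89 | 71% | 0.74 |
| 30 min | 15 min | 0.25 | 11% | 0.57 |
| 30 min | 30 min | 0.50 | 29% | 0.64 |
| 30 min | 60 min | 0.71 | 52% | 0.69 |

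The measures are equally sensitive by construction, so the differences between rows come from position alone. With slow decay the loss is modest.

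**The case against.** The strongest reply is that section 2.5.6 ranks nothing. It speaks of each modality's own arm contrast, both arms share the sequence, and section 2.6 plans no ROC analysis and no test across modalities. That is correct. A reader might infer that the trial intends to name the best marker, or that such a verdict is what would guide monitoring. The article says neither: what may inform monitoring protocols is the combined multidimensional profile. It would also be too strong to say that every modality has its own delay, or that the delays are fixed in minutes. Gaze and LSPT share a slot, and only the order is given.

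The protocol is also open that the post EEG follows the motor tasks, and sections 2.5.1 and 2.5.1.2 already call EEG changes multifactorial correlates and not definitive biomarkers. That caution concerns what EEG power means. It does not address how long after induction, or after what exercise, the EEG is recorded.

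Delay and decay are assumed throughout, and the article gives no basis for choosing among the scenarios. Figure 1, which is said to detail the collection moments, was not available here, and an article may leave time logging to the full protocol. Its absence is therefore not counted as a fault; logging is proposed only because it makes the narrower claim usable.

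What remains does not need a ranking. Even taken one modality at a time, a fair contrast late in the session does not measure ability to detect the state as it stood at the end of induction.

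**Conclusion.** The point holds as a limit on interpretation. The arm contrasts are valid at their own time points, and neither the design nor the sample size is at fault on this ground. What the design cannot support is reading those contrasts as the discriminatory power of each modality, or calling the examination simultaneous, because modality is fully aliased with elapsed time and intervening exercise.

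The direction of concern is that EEG, measured last, may look less sensitive than it is. The size cannot be established from the article. The illustrative fall in power at 20 minutes, from 81% to between 20% and 71%, depends on the assumed effect, delay, half-life and form of decay, and it leaves out any effect of exercise. The point is minor in severity, but it changes what the trial may conclude about detection.

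**What to change.** Keep the Phase 5 order and all planned tests. In section 2.5.6:

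- state that each modality's arm difference applies at its own position and delay after induction, and after any motor tests already completed;
- state that differences in discrimination between modalities cannot be separated from that position;
- drop the description of the examination as simultaneous.

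Record the clock time at the end of Phase 4 and at the start of each Phase 5 measure, and report the delay beside each result.

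The cost is a few logged times per session and a narrower claim about detection. The times are easy to take on the day and hard to recover afterwards.
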